**Methods:**

This is a double-masked randomised placebo-controlled superiority trial. University students identified with symptoms of visual stress, through use of a reading symptom questionnaire and mid-spatial frequency pattern glare test, will be recruited. Sample size for power of 90% at 5% significance, accounting for 10% dropout will be 65. Participants will be randomly assigned experimental and control coloured spectacle lenses to wear for six weeks followed by a two week washout period, prior to wear of the alternate lenses for a further six weeks with a two week washout period. Participants will compare both sets of spectacle lenses in a ‘head-to-head’ comparison after the secondary washout period, prior to choosing the preferred lenses for voluntary future wear. Long-term adherence to the preferred lenses will be assessed three months post-comparison. Researchers and participants will be masked to spectacle lenses worn throughout the duration of the trial. Reading performance will be assessed with both sets of lenses at various time points within the trial. A range of reading tests, reading symptoms and pattern glare evaluation will be used to monitor change in reading performance and visual stress symptoms during the trial.

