**Discussion:**

The study will evaluate the hypothesis that coloured spectacle lenses increase reading speed and reduce severity and frequency of reading symptoms in adults with visual stress.

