#### Inclusion criteria.

All participants shall be adult undergraduate students at Ulster University, aged 18–45-years. Participants shall be recruited in their first year of their current university degree. It is anticipated that the majority of participants will be young adults between the ages of 18–25, owing to the high prevalence of this age cohort attending undergraduate lectures. All included participants will be pre-presbyopic, i.e., not requiring a specific refractive error addition for near vision tasks/reading. Participants will be enrolled in the trial on the basis of presence of symptoms suggestive of visual stress, as determined by a reading symptom questionnaire and as detailed in Table 1.

**Table 1 pone.0309625.t001:** Recruitment criteria used to determine presence of visual stress.

Participants must satisfy at least one of the following sets of inclusion criteria:	
1. Presence of Significant Symptoms and Pattern Glare	Presence of any two symptoms with frequency scores ≥3, from the following: ‘Words/ letters look jumbled’. ‘Patterns seen in the white spaces between words/ letters’. Colours in the white spaces between words/ letters’. ‘Repeating words/ lines of text’. ‘Skipping words/ lines of text’. ‘Losing your place when reading’. ‘Words/ letters flicker when reading’. ‘Shimmering over the words/letters’. ‘Words/ letters wobble when reading’. ‘Words/ letters move’. ‘Words/ letters merge’. ‘Patterns/ shadows seen in text, e.g., rivers’. ‘Letters/ words stand out in 3D above the page’. ‘Letters/ words fade or darken on the page’. AND a pattern glare test score >3
2. Total Symptom Score >50%:	Summed total Likert symptom frequency score of 14-symptoms from 0-5 exceeds a 50% total score threshold (>35/70), when excluding 3 of the 17 Likert symptoms listed in the questionnaire, which may differentially diagnose other ocular abnormality (listed in brackets), which are: ‘Headaches when reading’. (Headache) ‘Eyestrain when reading’. (Asthenopia) ‘Words/ letters look blurred’. (Uncorrected Refractive Error)

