### Recruitment

#### Reading symptoms screening.

A reading symptom questionnaire was developed to screen large cohorts of undergraduate students in lecture theatres (see Supporting Information S2 File). There are currently no validated criteria used to diagnose visual stress [1,3]. Therefore, reading symptoms employed in the questionnaire were devised from symptoms of visual stress reported in the literature such as those proposed by a Delphi study [3] and the ‘Visual Stress Index’ [6]. The questionnaire includes 17-items and 6-point Likert scale with descriptors of symptom frequency (0 = never; 5 = always). Participants will be directed to consider their reading symptoms on a day-to-day basis when completing the questionnaire. Additionally, participants will be provided with a sample of crowded text in a foreign language, devoid of context, to consider when answering the questionnaire, if they are uncertain about the explanation of a particular reading symptom [6].

Questionnaire test-retest reliability was assessed on a sub-group of 115-undergraduate students through repeat issuing of the questionnaire six weeks after initial screening. Participants were blinded to motivation for retesting. High intraclass correlation coefficients were noted (0.91), with low bias of −1.99 (change in symptom scores with repeat measures, with a negative value indicating an increase on total summed symptom score on repeat) by Bland-Altman analysis [34]. Overall questionnaire internal consistency was also considered high by Cronbach’s alpha (α = 0.92) calculations. These findings confirm overall questionnaire test-retest acceptability for screening purposes.

Further questions exploring participants’ ocular and general health will be posed, as well as questions investigating presence of potential visual stress co-morbidities such as; headache [35,36]; formal diagnosis of migraine [37–40]; diagnosis of dyslexia [5,41,42] and/or diagnosis of specific learning difficulties and other general health complaints, known to also be managed with coloured filters [17,43–45].

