**Fig 2 pone.0309625.g002:**
[figure not shown]
Randomised control trial efficacy of coloured lenses for visual stress symptoms flowchart.

Upon completion of wear of both interventions a ‘head-to-head’ comparison of both coloured spectacles will take place. Participants will observe a crowded passage of text in a foreign language with both pair of spectacles under masked conditions. Participants will be asked to consider the reading symptoms they experience and to determine which pair of spectacles they find the greatest perceived benefit, irrespective of measures of reading speed and performance noted earlier in the trial. Participants will be advised to wear the preferred spectacles voluntarily, as they require. Participants will be contacted via telephone after three-months to assess long-term spectacle wear compliance and to assess if a sustained benefit from coloured lenses can be determined. Unmasking of participants shall not take place until the three-month follow-up to avoid influencing compliance levels in long-term spectacle wear.

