#### Secondary outcome measures: Symptom improvement, reading speed with further reading tests, pattern glare scores and long-term compliance with coloured lenses.

**Reading symptom change:** Prior to commencing wear of coloured lenses, participants will be asked to rate reading symptom frequency on the 6-point Likert scale initially used to recruit participants with symptoms suggestive of visual stress to the trial. After 10 minutes and six weeks of coloured lens wear, participants will be asked to repeat the symptom questionnaire. Additionally, after a two week washout period, participants will be asked to rate reading symptom frequency without the use of coloured lenses.

**Developmental eye movement (DEM) test:** The Developmental Eye Movement Test (DEM) Version 1 (Bernell Ltd, 1987), as summarised by Facchin [62] and Tanke et al. [63], was originally proposed to measure horizontal saccadic function of readers [64] but is now thought to more broadly assess oculomotor function whilst reading [62]. Horizontal and vertical reading speed will be measured. Number of omission, addition, transposition, and substitution errors will be noted and will be used to assist calculating adjusted horizontal and vertical reading speeds A ratio of adjusted horizontal:vertical reading speed will then be determined. The DEM will be completed with and without coloured lenses throughout the trial, owing to the low risk of a learning effect from repeat measures of a test comprising a random series of numbers.

**Test of word reading efficiency (TOWRE):** The Test of Word Reading Efficiency (TOWRE) 1st Edition (Pro-Ed Ltd, Austin TX, 1999) comprises a series of two standardised reading tests which independently assess a participant’s sight-word efficiency and phonemic decoding ability – as discussed further by Torgeson et al. [65]. Reading speed and number of errors made on both subtests will be recorded. A Total Word Efficiency Standard Score will be determined and compared to age-equivalent normative scores and percentiles [65,66]. Reading tests will be completed with and without coloured lenses as detailed in the Schedule of Enrolment.

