Repeated measures ANOVA testing will also assess reading speed on secondary reading tests employed in the trial with both ‘experimental’ and ‘control’ lenses, for the Adult Reading Test (2^nd^ Edition), The Test of Word Reading Efficiency (TOWRE) and the Developmental Eye Movement (DEM) test, at baseline, upon initial spectacle collection and after six-weeks of spectacle wear. Additionally, Friedman test will assess the median change of both interventions on low, mid and high-spatial frequency pattern glare test scores. Furthermore, McNemar’s Test of Proportions will investigate changes in reading symptom frequency scores at both the start and end of the six week spectacle wear period, with both spectacle lens interventions when compared to baseline reading symptoms reported.

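### Ordinal symptom scores are assigned to McNemar's test and compared only with baseline; no experimental-versus-control test of symptom scores is stated

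*Protocol article*

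**What the plan says.** All references are to the protocol article.

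- **Test.** Statistical analyses: "McNemar’s Test of Proportions will investigate changes in reading symptom frequency scores". It is applied at the start and end of each six-week wear period.
- **Comparator.** The same sentence ends "with both spectacle lens interventions when compared to baseline reading symptoms reported".
- **Scale.** Reading symptoms screening: "The questionnaire includes 17-items and 6-point Likert scale with descriptors of symptom frequency (0 = never; 5 = always").
- **Repeat ratings.** Secondary outcome measures: "After 10 minutes and six weeks of coloured lens wear, participants will be asked to repeat the symptom questionnaire". Symptoms are also rated before wear begins, and without lenses after washout.
- **Thresholds.** The only cut-points on this questionnaire are the eligibility rules in Table 1: two items scoring at least 3 (together with a pattern glare criterion), or "Summed total Likert symptom frequency score of 14-symptoms from 0-5 exceeds a 50% total score threshold (>35/70"). Neither is assigned to the outcome analysis.
- **Objective.** Abstract, Methods: "This is a double-masked randomised placebo-controlled superiority trial". Abstract, Discussion: the hypothesis is that "coloured spectacle lenses increase reading speed and reduce severity and frequency of reading symptoms in adults with visual stress". The Introduction repeats it.
- **Direct comparison of lenses.** After both wear periods, participants view text through both pairs and "determine which pair of spectacles they find the greatest perceived benefit" (Spectacle wear periods and washout).

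**The concern.** There are two separate faults, and the second is the graver.

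First, the test does not fit the data. McNemar's test counts people who switch between two states. A 0 to 5 item or a summed score must be cut before it can be used, and the size of each change is then discarded.

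Second, the comparison does not match the design. The control lens is there to absorb whatever would improve without an active tint: expectation, attention, the course of the academic term, familiarity with the questionnaire. Testing each lens against its own baseline leaves all of that in the result. A reader who sees a significant change on the experimental lens, and perhaps not on the control, may take this as evidence for the tint, although the difference between lenses was never tested. The symptom half of the stated hypothesis would then have no placebo-controlled test.

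**Working it through.** **What the article fixes.** It names the outcome (symptom frequency scores), the test (McNemar), the times (start and end of wear) and the comparator (baseline). It gives no effect size, SD or correlation for symptoms, so there is no symptom figure to reproduce.

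**Sample size used here.** The evaluable number is 59 (Sample size calculation), derived for reading speed. It reproduces from the printed partial eta squared. f² = 0.0355/0.9645 = 0.0368. With three measurements and correlation 0.5, λ = 59 × 3 × 0.0368/0.5 = 13.0 on 2 and 116 df, and power is 0.901.

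**Assumptions for the illustration.** Scores are bivariate normal, the shift is 0.3 to 0.5 SD, the correlation ρ is 0.5 to 0.7, and tests are two-sided at 0.05. The middle shift, 0.43 SD, is the one that gives a paired test about 90% power at ρ = 0.5.

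**Step 1: cost of dichotomising.** For the paired test on the score, the noncentrality is d√n / √(2(1−ρ)). At d = 0.43 and ρ = 0.5 this is 0.43 × 7.681/1 = 3.30 on 58 df, so power is 0.90.

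For McNemar, the best cut lies midway between the two means. At d = 0.43 and ρ = 0.5, the probability of crossing the cut is 0.264 towards improvement and 0.094 towards worsening. The sum is 0.358 and the difference 0.170. The normal approximation is z = (7.681 × 0.170 − 1.96√0.358) / √(0.358 − 0.170²) = (1.306 − 1.173)/0.574 = 0.23, so power is about 0.59. Simulation (40,000 runs) gives 0.62 uncorrected and 0.52 exact.

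Across the range (McNemar entries are uncorrected, with exact in brackets):

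| ρ | Shift (SD) | Paired score | McNemar, best cut | McNemar, cut 1 SD below the mean |
|---|---|---|---|---|
| 0.5 | 0.30 | 62% | 36% (27%) | 25% (18%) |
| 0.5 | 0.43 | 90% | 62% (52%) | 48% (39%) |
| 0.5 | 0.50 | 97% | 75% (66%) | 62% (53%) |
| 0.7 | 0.30 | 83% | 43% (34%) | 30% (22%) |
| 0.7 | 0.43 | 99% | 72% (64%) | 57% (47%) |
| 0.7 | 0.50 | nearly 100% | 84% (78%) | 72% (63%) |

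This compares two ways of testing one paired contrast. It measures what dichotomising loses, not the power of the analysis as written.

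**Step 2: cost of the baseline comparator.** Suppose that both lenses improve symptoms equally relative to baseline, so there is no lens effect. With n = 59, ρ = 0.5 among the three ratings, the cut at the baseline mean and exact McNemar:

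| Equal improvement (SD) | Experimental significant vs baseline | Experimental significant, control not | Direct lens-vs-lens McNemar significant |
|---|---|---|---|
| 0 | 3% | 2% to 3% | 3% |
| 0.30 | 26% | 14% | 3% |
| 0.43 | 51% | 17% | 3% |
| 0.50 | 65% | 16% | 3% |

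Uncorrected McNemar at 0.43 SD gives 61%, 16% and 5%. The direct comparison stays at or below its nominal level; the comparison with baseline does not answer the question about the tint.

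**The case against.** **Symptoms are a secondary outcome, and control results will be reported alongside.** True, and it lowers the severity. But two separate tests against baseline do not test the difference between lenses; the 17% above shows how the pair can mislead.

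**The head-to-head viewing compares the lenses directly.** It does, so it would be wrong to say that the lenses are never compared on anything symptom-related. It yields one preference, not a comparison of scores after six weeks of wear.

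**A cut-point may be left to the full protocol or analysis plan.** Fair; the missing cut is not a fault on its own. The article nevertheless chooses a test of proportions for scores and names baseline as comparator. An extension of McNemar's test to more than two categories is not named, and would still be against baseline.

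**Stronger readings that the article does not support.**
- A reader might infer that selecting participants for high scores guarantees a regression-to-the-mean improvement of calculable size. Symptoms are rated again before wear. If that rating is the baseline, much of the regression has already occurred. Eligibility also rests on either of two rules rather than one truncated score. In the retest sample of 115 students, scores rose on repeat (bias −1.99, where negative means an increase). No size can be given. That drift does show that scores can move over six weeks, the length of a wear period.
- A reader might infer item-by-item testing with near-certain false positives. The article does not say that items are tested separately, and items with a Cronbach's alpha of 0.92 are far from independent.
- A reader might take 0 to 70 as the outcome scale. That is the 14-item eligibility sum; all 17 items sum to 0 to 85 (17 × 5), and the article does not say which is analysed.

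**Conclusion.** The point holds. As written, an ordinal outcome is given a test for binary data, and the only stated comparison is with baseline, in a trial designed to show superiority over a placebo lens. That follows from the text and needs no assumption.

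The sizes do rest on assumptions, because the article gives no symptom effect, SD or correlation. Under those used above, dichotomising at the best cut lowers power from 62% to nearly 100% down to about 36% to 84%. An equal placebo response of 0.43 SD makes the experimental lens differ significantly from baseline in about half of trials.

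This should be fixed, but it is not a fault in the primary analysis: reading speed is the primary outcome, and the ratings needed for a proper symptom comparison are already scheduled.

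**What to change.** Replace the McNemar sentence with a between-lens analysis:

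- **Main symptom analysis.** Compare the summed symptom score at six weeks, experimental minus control, within person, allowing for period and sequence. A linear mixed model with lens, period and sequence as fixed effects and participant as random effect would do. Report the difference with a 95% confidence interval. This model would be new to the plan, which names repeated measures ANOVA for the reading tests.
- **Score.** State whether the 14-item sum (0 to 70) or the 17-item sum (0 to 85) is analysed.
- **Sensitivity analysis.** Wilcoxon signed-rank test on the paired lens difference.
- **Change from baseline.** Keep it as description for each lens, without a claim of efficacy, and say which rating is the baseline.
- **McNemar's test.** Use it only for a binary endpoint with a prespecified cut, compared between lenses.

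The cost is analysis wording only. The questionnaire is already repeated with lens wear, so no new data, visits or participants are needed. The change should be recorded before unmasking.

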### Data management

Data will be treated and stored in line with the amended Data Protection Act (2018). Reading symptom questionnaires used will have personal information attached to allow the researchers to identify participants with relevant visual stress symptoms, so that they can be contacted to participate in the trial. Once collected and analysed, each questionnaire shall be anonymised and assigned a unique participant identification number. Participants enrolled in the trial will be identified using their identification number assigned to their reading symptom questionnaire to ensure anonymity during data entry and analysis. All clinical and sensitive information written on hard-copy shall be stored in a secured filing cabinet, of which only the researchers can access. All electronic data will be stored on University-issued encrypted hardware on password-protected and encrypted data analysis programmes. Data management will comply with UK GDPR regulations. All collected data (electronic and hard copy, including data of participants who do not complete the trial) will be held for 10-years in line with university regulations. Anonymised data will be made available upon request upon cessation of the trial.

### Ethical considerations

The protocol (version 2.0; 21/10/22) has been approved by the Ulster University, School of Biomedical Sciences Ethical Filter Committee as of 28/10/2022 (Ref: FC-BMS-189). The trial is currently listed on ClinicalTrials.gov (Ref: NCT04318106). Participants will be informed that participation in the trial is voluntary and that they can withdraw their participation at any time. Informed consent will be ascertained through a written consent form provided alongside the reading symptom questionnaire (see supporting information S3 File– consent form). Risk of adverse incident from coloured spectacle lens wear is low, but will be monitored. In the unlikely event that an adverse incident occurs, it will be reported to the project’s chief investigator [name] and through Ulster University Research Governance protocols.

### Trial progress to date

1071 undergraduates at Ulster University have been screened for symptoms of visual stress, 171 undergraduates have met recruitment criteria and have been invited to participate in the trial. 60 participants are currently enrolled in the trial. Researchers plan to screen newly enrolled undergraduate students at the start of the 2024−25 academic year, to ensure adequate trial enrolment.

## Discussion

This study will be the largest randomised control trial investigating coloured lens efficacy in the management of visual stress in adults to date. Previous studies have been criticised for small sample sizes and being underpowered [1], therefore, it has been difficult to draw meaningful conclusions in relation to coloured lens efficacy. Additionally, this randomised control trial will be the first to assess reading symptoms and performance in a homogenous adult population, unlike previous investigations which have included both adults and children [13]. Evidence and guidance in relation to the practice of colorimetry from professional bodies in the United Kingdom is guarded [25,26], advocating for a large scale randomised control trial to take place prior to endorsing the practice. This is echoed in the findings of recent systematic reviews [1,21]. Therefore, we believe this trial is of high importance to inform best clinical optometric practice.

Researchers appreciate that the studied population will be somewhat homogenous in nature (young pre-presbyopic adult undergraduate students). This trial will explore coloured lens efficacy in a cohort of subjects with a relatively equitable baseline level of reading competence, as all undergraduate students enrolled will have to exhibit demonstrable English language competence to enrol at Ulster University. Whilst this will be beneficial at controlling for amount of reading demand each participant is expected to have, irrespective of whether a benefit of coloured spectacle lenses can be rejected or endorsed, the results of this trial may need be replicated in both paediatric and general adult populations, in future investigations. Additional factors such as gender and degree studied will not be controlled for as it there is no evidence to suggest that these factors are significant in relation to visual stress. As invitation to take part will be based on subjective-reported symptom severity, one may assume a certain degree of selection bias will exist. Researchers aim to reduce selection bias through randomisation and masking of participants. Additionally, whilst risk of ascertainment bias cannot be wholly negated, the exclusion criteria for this trial is relatively uncomplicated; ensuring that only those with binocular vision anomaly/amblyopia will be excluded. Furthermore, upon trial completion, researchers will report the number of participants identified with visual stress, number who attended baseline screening, failed exclusion criteria, dropped out and were lost-to-follow-up.

Irrespective of the results of this trial, we believe that the results generated from this investigation, will prove insightful in informing future optometric practice, whilst expanding the current evidence base on coloured lens efficacy in the management of visual stress. Recent position statements from the College of Optometrists UK [25] and the Association of Optometrists UK [27] suggest weaknesses in the current evidence surrounding the effectiveness of coloured lenses, and that the treatment of visual stress with coloured lenses remains controversial. Yet, over 300 optometry practices throughout the United Kingdom have an Intuitive Colorimeter™ and assess patients with reading difficulties and symptoms of visual stress [68] and the wearing of coloured lenses is not uncommon. In addition, optometric practices may offer alternative methods of visual stress assessment, such as coloured overlay assessment, and ‘ChromaGen’ contact lens fitting, amongst others. Whilst this study will not directly influence the management of visual stress with these alternative treatments, further knowledge on coloured filter efficacy will be uncovered from the results of this trial. The results of this study will provide the much needed evidence-base for optometrists, orthoptists and other practitioners assessing visual stress and reading difficulties. Results of this trial may steer the future direction of this area of optometric practice in relation to the practice of colorimetry and prescription of precision tinted lenses.
